## Background

It has been demonstrated that abdominal aortic aneurysm (AAA) screening of men aged 65-74 years reduces AAA mortality. Research at Viborg Hospital published in the British Medical Journal in March 2005 [1] shows that only 352 Danish men above the age of 65 require AAA screening to avoid one AAA rupture-related death in the subsequent 5-year period. Furthermore, it seems that the long-term economic efficiency of screening is at a level, which is generally considered cost effective, at least from a health care sector perspective [2-4]. Despite the clinical and economic evidence for the attractiveness of population screening, few national health care services have implemented permanent programs.

The majority of AAAs diagnosed by screening does not comprise a rupture risk due to being detected early, but nearly half expand to sizes requiring repair. However growth may be limited through smoking cessation [5,6], low-dose aspirin [7-9], statin treatment [10] and ACE inhibitor therapy [11] which will ultimately also reduce the increased cardiovascular risk of the affected patients [12].

International studies indicate that approximately 5-10% of men above the age of 60 show signs of peripheral arterial disease (PAD; ankle brachial systolic blood pressure index (ABI) <0.9) - a proportion which increases with age, and mainly non-symptomatic. Approximately 25-30% of these men will die from cardiovascular disease within a 5-year period, and an even higher proportion will need hospitalization due to cardiovascular disease. Cholesterol-lowering, smoking cessation, low-dose acetylsalicylic acid (aspirins), exercise, a healthy diet and blood-pressure control reduce the increased risks for cardiovascular disease by at least 20-25% [13-16]. So far, screening studies have neglected the interaction between PAD-screening and such general prophylactic efforts, and thus the benefit and cost effectiveness of screening may be underestimated.

In sum, well-documented health benefits may be achieved through prophylactic screening for cardiovascular disease. Advantages include fewer premature deaths and a reduction in the number of amputations and hospital admissions. Furthermore, hospital costs may be reduced by the decrease in admissions and in-hospital post-operative care.

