**Figure 1 F1:**
[figure not shown]
**Expected flow-chart concerning vascular screening (VIVA) for peripheral arterial disease, abdominal aortic aneurysm and hypertension**.

In the case of infrarenal aortic dilatation such findings are; i) pre-aneurysmatic (<24-30 mm<) or ii) aneurysmatic (≥30 mm). Dilatation <50 mm is controlled annually with ultrasound scanning and dilatation > 50 mm referred for consultation by a vascular surgeon. PAD may be reliable diagnosed with a portable ultrasound Doppler and blood pressure cuff. PAD is defined as ABI below 0.9 or above 1.4 and annual control is offered. In the case of suspected undiscovered hypertension (bloodpressure > 160/100) the patient is encouraged to see his family physician for further assessment and treatment.

During a training course, six project-nurses have been educated in the natural history of AAA, PAD and hypertension, instruction in life style changes and smoking cessation, blood sampling and bed side cholesterol measurement and the initiation of antiplatelet and lipid lowering medication. They were trained under supervision to measure ABI and perform ultrasound scanning of the aorta Independent examinations were only allowed, when the team-interobserver variation of aortic anterior-posterior diameter were below 2 mm, and ABI below 10%. The nurses operate in three mobile teams which will each be equipped with uniform portable Dopplers, blood pressure cuffs and portable ultrasound scanners and perform the screening sessions at the hospitals in the region. The project secretary will continually invite participants to their regional hospital using the names and address information from the randomization files.

Participants are informed that they should wear expedient footwear. The letter is accompanied by an option to refuse or reschedule in writing. Non-responders are re-invited once. Finally, enclosed with the invitation is a small questionnaire on smoking habits, anamnesis, walking-related pain (Walking Impairment Questionnaire), use of medicine, and the EUROQOL five dimensions (EQ5D) health questionnaire to obtain psychometric measures. This has recently been validated in Danish population norms [17]. Study participants commit to the program with a written consent using pre-printed consent forms.

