### Outcome

The primary outcome variable is all-cause mortality. The secondary outcome variables are cardiovascular mortality, AAA-related mortality, hospital services related to cardiovascular conditions and costs for such services, quality of life, and aneurismal progression. Major follow-up is planned after 3, 5 and 10 years. All-cause mortality, health care-related costs, cardiovascular and AAA-related mortality and cardiovascular hospital service are compared for the two groups.

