### Analysis of efficacy

Statistical analysis will be performed on an intention to treat basis. Risk ratios for all-cause mortality, cardiovascular mortality, AAA-related mortality and first cardiovascular event in the two groups will be estimated by Cox-regression. In addition, the numbers of hospital services related to cardiovascular conditions will be compared between the two groups by student's t-test. Quality of life between controls, non-attenders, attenders without positive finding, and attenderswith AAA or PAD will be compared at baseline univariately and multivariately adjusted for age, civil status and co-morbidity, and prospective data from baseline, after 3, 5 and 10 years will be compared by MANOVA. Aneurysmal progression (growth rate) will be transformed by the natural logarithm and evaluated in subgroups by univariate and multivariate linear regression analysis. SPSS 15.0, STATA 12.0 and PEPI will be used for the analysis.

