### Power and expected benefit

The needed sample size estimation was done by the following assumptions:

The prevalence of AAA and PAD is 4% and 8% respectively. The five year mortality risk in case of AAA or PAD is 28% oppose to 15% in the control group. Statin-lowering or antiplatelet medication can be initiated in one-third of the diagnosed men with PAD or AAA and causes a relative all cause mortality risk reduction of 20%. AAA-related death within five years is 1% but screening reduces this with 50%. The expected screening attendance is 75%

If so, the needed sample size is 2 × 23,604 (5% significance level and 90% power) and approx. 250 lives will be saved. If the ten year mortality in the control group is 36% [3], and if the relative risk is maintained, the needed sample size is 2 × 7,500, corresponding to 2.5% absolute mortality risk reduction and 590 lives saved corresponding to 40 men needed to screen to prevent one death.

These calculations must be considered to be conservative and the potential benefit by diagnosing new hypertensives is not included.

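### The log of the aneurysm growth rate does not exist for observed rates of zero or below, which the planned annual scans will produce

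*Protocol article*

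**What the plan says.** The Outcome section lists, among the secondary outcomes, "quality of life, and aneurismal progression". The Analysis of efficacy section fixes the method: "Aneurysmal progression (growth rate) will be transformed by the natural logarithm and evaluated in subgroups by univariate and multivariate linear regression analysis". The variable to be logged is therefore the growth rate, not the diameter. No offset, floor or alternative scale is given.

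Two design features bear on the values that rate can take. Both stand in the screening-program section, after Figure 1.
- Rescanning: "Dilatation <50 mm is controlled annually with ultrasound scanning".
- Measurement: nurses could examine independently "when the team-interobserver variation of aortic anterior-posterior diameter were below 2 mm".

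The Background says of screen-detected aneurysms that "nearly half expand to sizes requiring repair", so more than half do not. It adds: "However growth may be limited through smoking cessation", and names several drug treatments as well.

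**The concern.** A growth rate is a difference between two diameters, each measured with error, divided by time. When true growth over the interval is similar in size to the error, some observed rates will be zero or negative even if no aorta shrinks. The planned transformation cannot represent these men.

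Two things follow if the sentence is applied as it stands. First, a man without a logarithm is missing from the regression. That loss depends on the outcome itself: it takes away the lowest rates, raises mean growth, and takes more men from slower-growing subgroups. Second, men just above zero stay in with undue influence. Against 2 mm/year, a man at 4 mm/year differs by ln 4 − ln 2 = 0.69, but a man at 0.1 mm/year differs by ln 2 − ln 0.1 = 3.00, and most of that may be measurement noise.

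Little or no growth is also the result that the Background hopes prophylaxis will bring, so the scale fails where the clinical interest lies.

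**Working it through.** The protocol article gives no growth distribution, precision or power figure for progression, so there is no stated result to reproduce. The check asks how often the logarithm fails and what dropping those men does.

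**Inputs from the document.** Annual rescans below 50 mm; interobserver variation below 2 mm (metric undefined); about 50,000 men, half invited; attendance 75%; and "The prevalence of AAA and PAD is 4% and 8% respectively". Expected men with AAA: 25,000 × 0.75 × 0.04 = 750.

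**Assumptions, not in the document.**
- True annual growth g is gamma distributed, so never negative, with mean/SD of 1/1, 2/1.5 or 3/2 mm/year.
- Measurement error is normal and independent, with SD s of 0.7 or 1.0 mm per scan. If 2 mm is read as 1.96 SD of the difference between two readings, s = 2/(1.96 × √2) = 0.72. The value 1.0 allows for more error in routine use.
- Each man's rate comes from his first and last scan, T years apart.

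**Formula.** The observed rate is r = g + error, where the error SD is σ = s√2/T. For mean 1 and SD 1 (exponential growth), P(r ≤ 0) = 0.5 − exp(σ²/2) × Φ(−σ):
- T = 1, s = 0.7: σ = 0.990; 0.5 − 1.632 × 0.161 = 0.237
- T = 1, s = 1.0: σ = 1.414; 0.5 − 2.718 × 0.0786 = 0.286
- T = 3, s = 0.7: σ = 0.330; 0.5 − 1.056 × 0.3707 = 0.109
- T = 3, s = 1.0: σ = 0.471; 0.5 − 1.1175 × 0.3187 = 0.144
- T = 5: σ = 0.198 and 0.283; results 0.070 and 0.095

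**Simulation of all three growth settings** (2 million men per cell; ranges run from s = 0.7 to s = 1.0; rates in mm/year). Each growth column gives the share of rates at or below zero, then the mean rate in the men kept.

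| Interval | Growth 1/1 | Growth 2/1.5 | Growth 3/2 | Difference in means kept, 2 vs 1 (true 1.0) |
|---|---|---|---|---|
| 1 year | 24-29%; 1.52-1.79 | 11-16%; 2.31-2.53 | 5-9%; 3.20-3.37 | 2.31 − 1.52 = 0.79; 2.53 − 1.79 = 0.74 |
| 3 years | 11-14%; 1.15-1.22 | 2.4-4.1%; 2.06-2.10 | 0.7-1.4%; 3.02-3.04 | 0.91; 0.88 |
| 5 years | 7-10%; 1.08-1.12 | 1.1-1.9%; 2.02-2.04 | 0.3-0.5%; 3.01-3.02 | 0.94; 0.92 |

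The simulation agrees with the formula in the 1/1 column. Recording diameters in whole millimetres raises the one-year share to about 10-40%.

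**On the planned log scale.** Compare mean growth of 2.0 with 1.5 mm/year at the same relative spread, so that the true geometric-mean ratio is 0.75. Among the men kept it is 0.80-0.83 at one year and 0.76-0.77 at three. If the 2 mm is instead the SD of the difference between two readings, it is 0.86 and 0.78. With less spread between men (SD 1.0 at mean 2.0), the three-year ratio is 0.74-0.75, so there is then no attenuation to speak of.

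**In men.** If all 750 had a rescan, one-year rates would lose about 750 × 0.05 = 38 to 750 × 0.29 = 218. Three-year rates would lose about 750 × 0.007 = 5 to 750 × 0.14 = 105.

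**The case against.** The best reply is that a condensed article leaves the handling of awkward values to a full protocol or analysis plan, and that the planned horizons of 3, 5 and 10 years make the loss small. Much of this stands. At 2 mm/year or more, three-year rates lose only a few percent and the log-scale ratio hardly moves. It does not stand for slow growers, who still lose 11-14% at three years, or for men with a single rescan. Nor is the matter only an omission: the article fixes a scale that fails on foreseeable data, and an offset would make the estimates depend on an arbitrary constant.

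A reader might infer more than the document supports:
- **That the plan deletes slow growers.** It prescribes no exclusion; deletion is what happens if nothing is added. Some of the men lost would be true growers whose growth was hidden by error.
- **That a treatment effect on growth is diluted.** The text speaks of subgroups and names none.
- **That men with two scans and men with ten get equal weight.** How each man's rate is derived, and whether the regression is weighted, is not stated.
- **That one-year figures describe the whole analysis.** They are the worst case.
- **That 2 mm is the trial's measurement error.** It is a ceiling that nurses had to meet in training.
- **That the randomised comparison suffers.** Controls are not invited to scanning, and progression is not among the outcomes that the Outcome section compares between the two groups.

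**Conclusion.** The point holds, in a limited form. The named transformation is undefined for values that the protocol's own scanning scheme will produce, so the analysis cannot be carried out on all men as written. Under the assumed growth and error, about 5-29% of rates are affected over one year, about 1-14% over three and 0.3-10% over five. If those men are dropped, a true difference of 1.0 mm/year (1 vs 2) becomes about 0.74-0.79 at one year, about 0.9 at three and 0.92-0.94 at five. Those are differences of arithmetic means; on the planned log scale the distortion at three years is slight unless growth is slow or error large.

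That the logarithm fails is certain. The size is not, because it rests on growth and error figures that the document does not give. The damage is confined to a secondary analysis within the screened group, but the repair is cheap enough that it should be made.

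**What to change.** Replace the log growth rate with a linear mixed model on all serial diameters, or on ln(diameter), which always exists. Give each man a random intercept and slope, and test covariate × time terms as effects on growth. This keeps men with zero or negative observed change and lets men with more scans contribute more information.

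At minimum, analyse the untransformed rate so that these men are kept, and state how each man's rate is derived.

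The cost is a change of wording and slightly more analysis work. No new data are needed.

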### Analysis of cost-effectiveness

The program cost per invited will be estimated using a micro-costing approach for the intervention (invitations, screenings, follow up scans). Relevant resource utilization at hospitals (surgical procedures, admissions, outpatient visits etc.) will be extracted from the National Patient Registry and valued using tariffs of the Diagnosis-Related Grouping (DRG) case-mix system. Participants' time and transportation costs will be estimated from a prospective within-sample study of about 1,000 participants using a questionnaire.

Health-related quality-adjusted life will be estimated for each individual assuming that baseline quality of life follows that of an age- and sex-matched population norm [17]. For persons detected with and/or treated for cardiovascular disease estimates of decrements in quality of life will be adapted from the literature and applied.

The net present values of costs, life years gained and QALYs gained will be compared between randomization groups [18]. The incremental ratios of costs per life-year gained and costs per quality-adjusted life year (QALY) gained will be estimated using nonparametric bootstrapping; for their interpretation the net benefit framework will be used to present cost-effectiveness acceptability curves [19,20].

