### Follow-up and data collection

All positive findings are subject to clinical monitoring to provide a reassuring context for the communication of the finding and its consequences. In the case of PAD the participant is informed of the relatively positive prognosis of leg survival and the need to initiate suitable prophylactic measures including walking/exercise, smoking cessation, low-fat diet, aspirin and statin treatment. Cholesterol levels are measured. If it exceeds 4.0 mmol/l, cholesterol is unlikely to fall below 3.5 mmol/l following relevant diet changes and, consequently, the patient is given a prescription for 40 mg simvastatin/day. Annual follow-up with ABI measurement is offered. The EQ-5D is fulfilled upon visit and in connection with any follow-up.

In the case of AAA the aorta is reassessed, the finding is stored digitally and the calcification degree and mural thrombus is determined. Information regarding the natural history of AAA is delivered and the need to initiate suitable prophylactic measures including exercise, smoking cessation, low-fat diet, aspirin and statin treatment in accordance with the guideline from the European Society of Cardiology 2007. If the AAA exceeds a diametre of ≥ 50 mm, the patient is referred for CT scan and assessment by a vascular surgeon to further surveillance or surgery. If the AAA is below 5 cm, annual control with ultrasound scan is offered. The EQ-5D is fulfilled upon visit and in connection with any follow-up, as well as annually after AAA surgery.

Data from the screening procedure are collected in a large database. Information concerning deaths, including-date and cause of death, is obtained from the Civil Registration System. Information on visits to outpatient clinics and hospital admissions caused by cardiovascular conditions including amputations is obtained from the National Patient Registry. From the Danish Causes of Death Registry, data on cause of death are collected. The information is classified according to cause; AAA-related or cardiovascular.

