### Randomization

Civil registration numbers and patient data are obtained from national registries. Randomisation is stratified by municipalities, as the prevalences of the diseases are expected to differ in this relatively large region. The Region consists of 19 counties covering more than 13,000 km2, which includes some of the largest Danish cities in the eastern part, as well as rural areas in the western part of the region. The stratification furthermore ensures a minimum of time span between randomisation and invitation as local screening units individually can report back to the central randomisation office about their time schedule.

Person-data are imported to Epidata and Epi-info 6, where randomisation occurs by giving each subject a random number from 1-100, persons with a number above 51 are allocated to the intervention arm i.e. half of subjects are invited to participate in screening and half of subjects act as controls (as no permanent screening programme exists in Denmark).

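### The QALY rule takes utility away on detection, which is systematic in the invited arm only; any disease-state part of the decrement biases the QALY difference against screening

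*Protocol article*

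**What the plan says.** All references are to the protocol article.

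- *Analysis of cost-effectiveness* builds each man's QALYs "assuming that baseline quality of life follows that of an age- and sex-matched population norm". It then adjusts: "For persons detected with and/or treated for cardiovascular disease estimates of decrements in quality of life will be adapted from the literature and applied". The result feeds a randomised comparison: "The net present values of costs, life years gained and QALYs gained will be compared between randomization groups".
- *Randomization* fixes who is searched for disease: "half of subjects are invited to participate in screening and half of subjects act as controls".
- *Background* describes PAD as "a proportion which increases with age, and mainly non-symptomatic".
- *Power and expected benefit* assumes: "The prevalence of AAA and PAD is 4% and 8% respectively". Expected attendance is 75%.
- *Follow-up and data collection* has the trial measuring utility itself in men with a positive finding: "The EQ-5D is fulfilled upon visit and in connection with any follow-up". *Analysis of efficacy* plans a quality-of-life comparison of controls, non-attenders, attenders without a finding and attenders with AAA or PAD, at baseline and prospectively.

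The cost-effectiveness section does not say whether the literature decrement stands for living with the disease or for the consequences of being diagnosed and treated. It also does not link the QALYs to the measured EQ-5D.

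**The concern.** Randomisation gives both arms the same expected burden of AAA and PAD. What differs is whether the disease is found, because finding it is the intervention. A utility rule triggered by detection therefore gives different values to two men in the same state of health, depending on allocation.

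The norm adds a second problem. A population average should already include men with unrecognised disease. Subtracting a disease decrement from that average, when screening uncovers the disease, counts it twice, and this happens mainly in the invited arm.

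Cost-effectiveness is one of the two parts of the stated objective. The expected QALY gain per invited man is small, because it is spread over everyone invited. A small utility loss applied to nearly a tenth of them for years can be of similar size.

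**Working it through.** **Nothing to reproduce directly.** The article gives no utility, decrement, QALY or cost-effectiveness ratio. What follows is a scale check against the survival benefit that the article plans for, taken at face value.

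**Inputs from *Power and expected benefit*:** AAA 4%, PAD 8%, attendance 75%, 23,604 men per arm, about 250 lives saved at five years, 2.5% absolute reduction at ten years. Check of the yardstick: 250 / 23,604 = 1.06%, and 0.025 × 23,604 = 590, which agrees with the 590 lives stated.

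**Assumptions (not in the article):** decrement d of 0.01 to 0.05; norm utility 0.80; no overlap of AAA and PAD; averted deaths spread evenly over the horizon H; no discounting; at first, no detection or treatment of such men in the control arm; and d wholly a disease-state decrement.

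**Step 1, share screen-detected.** 0.75 × (0.04 + 0.08) = 0.09, or 0.09 × 23,604 ≈ 2,124 men.

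**Step 2, survival gain per invited man** = absolute reduction × H/2 × 0.80.
- Five years: 0.0106 × 2.5 × 0.80 ≈ 0.021 QALY.
- Ten years: 0.025 × 5 × 0.80 = 0.10 QALY.

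**Step 3, artefact per invited man** = 0.09 × (1 − s) × d × H, where s is the share of such men who are also detected or treated in the control arm.

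| d | 5 years, s = 0 | % of gain | 10 years, s = 0 | % of gain | % of gain at s = 0.5 (5 y / 10 y) |
|---|---|---|---|---|---|
| 0.01 | 0.0045 | 21 | 0.009 | 9 | 11 / 4.5 |
| 0.02 | 0.009 | 42 | 0.018 | 18 | 21 / 9 |
| 0.05 | 0.0225 | 106 | 0.045 | 45 | 53 / 22.5 |

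**Step 4, decrement at which the artefact equals the gain (s = 0).**
- Five years: 0.0212 / (0.09 × 5) ≈ 0.047.
- Ten years: 0.10 / (0.09 × 10) ≈ 0.11.

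**Step 5, sensitivity.**
- If overlap brings combined prevalence to an assumed 10%, the detected share is 7.5% and the five-year range becomes 18% to 89%.
- The formula charges d for the whole horizon and ignores deaths. With the article's 28% five-year mortality in diseased men spread evenly, mean time alive is 5 × (1 − 0.28/2) = 4.3 years. The five-year artefact falls by 14%, so 106% becomes about 91%.
- If only a fraction f of d is disease state, every artefact is multiplied by f. At f = 0 it is zero.

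Under all these variations the artefact is either zero or against screening.

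**The case against.** **Part of the decrement may be real.** Worry after a diagnosis, medication and surgery are consequences of screening, and their utility cost belongs in the invited arm. This stands. A reader might infer that the QALY result is biased whatever the decrement means. The article does not support that, because it leaves the decrement undefined, and a pure diagnosis or treatment effect would produce no artefact.

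**The rule is not restricted to one arm.** Controls who are diagnosed clinically or treated receive the decrement too. The population has no exclusions, so known cases are in both arms. *Background* expects 25% to 30% of men with PAD to die of cardiovascular disease within five years and an even larger share to be admitted to hospital. This also stands, and the s = 0 figures are an upper case. It reduces the asymmetry without removing it: until his disease comes to light, a control stays at the norm while his screened counterpart does not.

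**The article is condensed.** Decrement values may well be in a full plan. The trigger for applying them, however, is stated here, and the trigger is the problem.

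**Quality of life is measured and compared with controls.** This is true, but as written that analysis does not feed the QALYs.

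**The costs might seem to have a matching error.** Preventive drugs and family-physician visits are not named among the cost items, and a reader might conclude that costs are wrong as well. The article does not exclude them. *Outcome* refers to health care-related costs, and a full costing list is detail that an article may leave out. No finding is made on costs.

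**Conclusion.** The point holds conditionally. As stated, the rule makes utility depend on detection, and systematic detection occurs in one arm. To the extent that the decrement represents the disease state, screen-detected men lose utility that equally diseased undetected controls keep, and the QALY difference is biased against screening.

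The size is unknown, because no decrement is given. On the assumptions listed, it is 21% to 106% of the expected survival gain at five years and 9% to 45% at ten, and half of that if half of such controls are also detected or treated.

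A reader might infer that the artefact would make the QALY gain negative. That does not follow from the documents. At five years it needs an assumed decrement above about 0.047 with no control-arm detection. At ten years it needs about 0.11, outside the range considered. What is shown is that a modest decrement could distort the cost-utility result materially. That justifies fixing the rule before the QALYs are calculated.

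**What to change.** 1. **Base case.** Apply disease decrements only to health states or events ascertained in the same way in both arms from the National Patient Registry, for example cardiovascular admission, amputation or AAA surgery. The section already draws on this source for costs: "Relevant resource utilization at hospitals (surgical procedures, admissions, outpatient visits etc.) will be extracted from the National Patient Registry".
2. **Separate diagnosis term.** Carry any effect of being told of a finding as its own term, so that true labelling harm is counted once and visibly. Inform it from the EQ-5D comparison that includes controls (*Analysis of efficacy*). An uncontrolled change within screened men would mix the effect of detection with ageing, disease progression and selective follow-up.
3. **Sensitivity analyses.** Report the QALY difference and the acceptability curves with and without a decrement for asymptomatic screen-detected disease.
4. **Wording.** State for each literature decrement whether it represents the disease state, the diagnosis or the treatment.

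Cost: a change of wording and modest extra analysis on data already planned. The downside is that the base case then relies on the separate term to capture real harm from diagnosis. The EQ-5D data available from controls should therefore be confirmed before that term is fixed.
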